**Figure 1 F1:**
[figure not shown]
Treatment schedule.

### Study objectives

The primary objective is to evaluate the efficacy of TACE plus Sorafenib compared to TACE plus placebo in patients with HCC before LTx. The primary endpoint is the TTP based on radiological assessments, defined as the time from the date of randomization to disease progression. In the absence of a TTP event, TTP time will be censored at the date of last disease assessment. The secondary efficacy objectives are to assess the number or patients reaching LTx, disease control rates, 1- and 2-year OS after LTx, progression-free survival, number of TACE in each arm, quality of life, safety and toxicity.

### Randomization and treatment

Patients will be randomly assigned on a 1:1 basis in a blinded fashion to the Sorafenib 400 mg or placebo. To accomplish this, a computer generated randomization list, which is provided to the Pharmacy at University Hospital Heidelberg, will be prepared by the Patient and Clinical Study Center (PaSZ) at NCT.

When ordering study medication, the investigator will receive a set of sealed envelopes, via the distributing pharmacy, one for each randomization number. An identical set of sealed envelopes will be held in safe and confidential custody at the NCT. These envelopes contain information on the subject's trial medication and are to be opened only under circumstances in which it is medically imperative to know what the subject is receiving. Date and reason for opening a sealed envelope must be documented. If possible, the investigator will confer with the safety officer before unblinding. The randomization envelopes are not to be opened by the investigator at the end of the trial. All envelopes will be collected by the site monitor at the end of the trial.

### Investigation schedule and follow-up

Pre-treatment evaluation for all patients includes demographic data, medical history, physical examination, co-morbidities, and concomitant medications, complete lab (CBC, hemoglobin, hematocrit, sodium, potassium, magnesium, calcium, chloride, BUN, creatinine, ASAT, ALAT, GGT, alkaline phosphatase, total bilirubin, direct/indirect bilirubin, lipase, amylase, lactat dehydrogenase, total protein, albumin, glucose, bicarbonate, autoantibodies, PTT, PT and INR, tumor marker AFP, hepatitis virology, TSH, fT3 and fT4) and radiological studies to meet the inclusion criteria. During treatment, patients will visit the outpatient clinics every two weeks during the first month and every four weeks thereafter. At this visits the aforementioned laboratory measurements, physical examination, concomitant medication, vital signs, Karnofsky status and adverse events will be recorded in the electronic case report form (eCRF). During each monthly visit, patients will be provided with the required monthly amount of study product (or placebo) and are asked to return the emptied study boxes to survey compliance. Four weeks after each TACE imaging study, a CT scan of the thorax and abdomen as well as analysis of tumor marker AFP will be performed. At end of treatment due to progression or day of LTx, the aforementioned laboratory measurements, physical examination, concomitant medication, vital signs and adverse events will be recorded, imaging studies and AFP level analysis performed. In the first year after treatment, patients will be seen every 3 months for clinical assessment, laboratory analysis and imaging studies. Follow-up data of OS will be evaluated after 12 and 24 months after end of treatment or LTx.

### Assessment of quality of life

Measurement of quality of life is one of the secondary objectives of the trial. OS, return to previous employment, persistence of symptoms, the ability to perform appropriate activities and to care for oneself are criteria applied in the three questionnaires used in this study. The EORTC QLQ-C30 is a general measure of quality of life in cancer patients. It consist of nine multi-item scales: five functional scales (physical, role, cognitive, emotional, and social); three symptom scales (fatigue, pain, and nausea and vomiting); and a global health and quality of life scale [15]. Specific symptoms (dyspnea, insomnia, anorexia, constipation, and diarrhea) are measured as single items. To assess disease-specific symptoms for patients with HCC the HCC specific module (QLQ HCC18) will be used in this study [16]. Patients will complete the quality of life questionnaires at the baseline visit, four weeks after each TACE and at the end of study at day of LTX or tumor progression. Health-related Quality of Life (HQoL) subscales and single item sub-scores will be summarized by the mean and median for each arm and plotted by time. HQoL data will be analysed using ANCOVA techniques. Detailed biometric analysis will be defined in the statistical analysis plan (SAP) which has to be authorized before unblinding by the biometrician, the sponsor, and the leading clinical investigator (LKP).

### Sample size calculation

The sample size calculation is based on the detection of significant differences in TTP, the primary endpoint parameter of this trial, assuming that median TTP is 4.5 months for the placebo-arm and 7.5 months for the sorafenib-arm [11]. A total of 120 TTP events are required for a log-rank test with an overall one-sided significance level of 0.05 and power of 0.875. Applying a 1:1 randomization, a planned accrual period of 24 months, and a follow-up period of 9 months, it is estimated that 136 patients will be needed. From the experience gained at the surgery department it can be expected that about 50% of the patients will drop-out after randomization. These patients do not contribute any information to the primary endpoint of this study. In order to accommodate for a maximum drop-out rate of 50% the total sample size is therefore increased to 208.

A design with 2 stages (one interim analysis and the final analysis) has been chosen. The critical values and the test characteristics of the group sequential test design were calculated for the O'Brien and Fleming stopping rule. The nominal significance levels for the interim analysis (planned to be conducted when 60 events have occurred) and final analysis are 0.0051 and 0.0484 respectively. The final analysis will take place when approximately 120 events are observed.

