## Background

Hepatocellular carcinoma (HCC) is the sixth most common cancer worldwide with more than 1 million deaths annually [1]. The prevalence of Hepatitis B and C with consecutive liver cirrhosis and HCC tumor growth leads to an increasing incidence of HCC especially in Europe and the USA [2]. HCC develops in a cirrhotic liver in 80% of cases, with an annual incidence of 2–6% for hepatitis B virus carriers and 3–5% for hepatitis C virus infected individuals. Two decades ago, the prognosis of HCC was devastating with most patients dying within the first year after diagnosis irrespective of their treatment [3]. The development of standardized surveillance strategies and the introduction of the Barcelona-clinic liver cancer classification (BCLC) for clinical management of HCC have significantly improved outcome. In industrialized countries 30–40% of patients are now being diagnosed at initial stages when curative treatments can be optimally applied. 5-year overall survival (OS) after resection, liver transplantation (LTx) or percutaneous treatment in select candidates reaches 50% to 70% in patients with early HCC (single or 3 nodules ≤3 cm) [1]. Untreated patients at an intermediate stage (multinodular asymptomatic tumors without an invasive pattern) achieve a median OS of 16 months. Locally ablative treatments provide good results (5-year survival 40–50%) for these patients but cannot achieve response rates and outcomes comparable to surgical therapy, even when applied as a first line treatment.

LTx is the best treatment option for patients with small multinodular tumors or those with advanced liver dysfunction. It has the potential to cure the tumor and the underlying liver disease. Tumor size at the time of LTx as defined by the Milan criteria (single tumors ≤5 cm or 3 nodules ≤3 cm) has been established as a prognostic factor [4]. In tertiary referral centers applying these criteria, survival is ~70% at 5 years, with a recurrence rate of less than 15% [5]. The shortage of donors still curtails the potential benefits of LTx. In western countries, tumor progression occurs in 20–50% of cases on the transplant waiting list.

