### Study design

The HeiLivCa trial is a prospective, multi-center, placebo-controlled, randomized, double-blind clinical trial with two parallel treatment groups receiving TACE plus sorafenib or TACE plus placebo. Patients in both groups will be treated with a maximum of four TACE procedures. For TACE carboplatin will be used as chemotherapeutic drug and lipiodol as embolizing agent. Four weeks after TACE, response will be evaluated by CT-imaging. Study medication will be stopped at progression. For patients without progression, treatment with sorafenib or placebo will be continued until LTx. All patients will be followed for 24 month after end of treatment. The duration of the overall trial is expected to last approximately 48 months. The actual duration of trial may vary due to the availability of patients meeting the criteria after registration for LTx. (Figure 1)

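### The projection of 120 progressions from 136 patients in 24+9 months has no term for transplantation, and the text does not say whether the 50% drop-out covers it, so the event count and timing are unsupported

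*Protocol article*

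**What the plan says.** Under Sample size calculation, the planning assumption is that "median TTP is 4.5 months for the placebo-arm and 7.5 months for the sorafenib-arm". The next statement is "A total of 120 TTP events are required for a log-rank test", and the design values are given as "overall one-sided significance level of 0.05 and power of 0.875". The patient number follows: "Applying a 1:1 randomization, a planned accrual period of 24 months, and a follow-up period of 9 months, it is estimated that 136 patients" are required. The total is then raised to 208 to allow for a drop-out of up to 50%, put down to local experience; these patients are said to give no information on the primary endpoint. On timing: "The final analysis will take place when approximately 120 events are observed". No calendar limit is attached.

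Under Study design: "For patients without progression, treatment with sorafenib or placebo will be continued until LTx". The same section expects the whole trial to last about 48 months and allows that this may vary. Study objectives makes the number of patients reaching LTx a secondary endpoint. It censors TTP at the last disease assessment when there is no event, and does not mention LTx. Investigation schedule and follow-up continues imaging every three months in the first year after treatment.

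**The concern.** In this population, leaving the at-risk period without progressing is the intended outcome: patients are enrolled because they may be transplanted. LTx therefore competes with the primary event. A projection in which 120 of 136 contributors progress (88%) leaves room for at most 16 (12%) to be transplanted progression-free without later recurrence.

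The trial enrols 208, so the question is whether the extra 72 absorb the LTx loss. The text attributes them to drop-outs who contribute nothing. It neither breaks the 50% down by cause nor says whether transplanted patients are among them. A patient censored at LTx does contribute time at risk, so the wording does not clearly describe such patients.

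The final analysis is tied to an event count alone. If that count is late or unattainable, the plan as written gives no rule for when the final analysis happens or at what level it is tested.

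**Working it through.** **Inputs from the document.** Medians 4.5 and 7.5 months (HR = 4.5/7.5 = 0.60); one-sided 0.05; power 0.875; 1:1 allocation; accrual A = 24 and follow-up F = 9 months; 136 patients before and 208 after the drop-out allowance; 50% drop-out contributing nothing.

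**Assumed, because the document gives no figure.** Exponential time to LTx with a median between 36 and 6 months, the same in both arms, and LTx ending the risk of a TTP event.

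**1. Events and power.** Schoenfeld: d = 4(1.645 + 1.150)²/(ln 0.6)² = 4 × 7.81/0.261 ≈ 120. In reverse, power = Φ(0.5108·√d/2 − 1.645), which gives 0.876 at d = 120. Both stated figures reproduce.

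**2. The 136.** With exponential TTP, uniform accrual and no loss other than the data cut, P(event) = 1 − (e^(−9λ) − e^(−33λ))/(24λ).
- Placebo, λ = ln 2/4.5 = 0.154: 0.934.
- Sorafenib, λ = ln 2/7.5 = 0.0924: 0.825.
- Mean 0.880; 120/0.880 = 136.4, and 136 × 0.880 = 119.6.

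The figure comes out with zero removal before progression.

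**3. The stated drop-out.** 208 × 0.5 = 104 contributors, fewer than the 120 events required. By month 33: 104 × 0.880 = 91.5 events, power 0.79. No LTx loss is in this figure; it follows from the drop-out statement alone.

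**4. Adding LTx.** With LTx hazard μ = ln 2/(median time to LTx):

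P(event) = λ/(λ+μ) × [1 − (e^(−9(λ+μ)) − e^(−33(λ+μ)))/(24(λ+μ))].

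Example, median 12 months (μ = 0.0578): 0.706 for placebo and 0.572 for sorafenib, mean 0.639.

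Expected events by month 33, with power at that count:

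| Assumed median to LTx (months) | Mean P(event) | 104 contributors | 136 contributors | All 208, LTx the only loss |
|---|---|---|---|---|
| none | 0.880 | 91 (0.79) | 120 (0.87) | 183 |
| 36 | 0.783 | 82 (0.75) | 107 (0.84) | 163 |
| 24 | 0.742 | 77 (0.73) | 101 (0.82) | 154 |
| 12 | 0.639 | 66 (0.67) | 87 (0.77) | 133 |
| 9 | 0.584 | 61 (0.64) | 80 (0.74) | 122 |
| 6 | 0.497 | 52 (0.58) | 68 (0.68) | 103 |

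The power values are the single-look approximation at one-sided 0.05.

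**5. Ceilings.** If all 208 contribute, 120 events are out of reach once more than 88 patients (88/208 = 42%) are transplanted progression-free without recurrence. In the last column, a 9-month median means about 38% are transplanted before progression, and 120 is still met. At 6 months, the 208 level off at about 106 events however long the trial runs.

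**The case against.** The strongest reply is that 136 is only an intermediate step. The trial enrols 208, and if the 50% was meant to cover LTx with little other loss, the last column applies: 120 events arrive by month 33 down to a median of about 9 months. This stands, and it means that the 12% ceiling applies to 136 contributors and not to the trial as enrolled. It does not settle the matter, because the text never says that the 50% includes LTx. Taken at its word, the 50% leaves 104 contributors whatever the cause of loss.

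A reader might infer that the 87.5% power is wrong. The document does not support that. The final analysis is event-driven and 0.875 is correct at 120 events under proportional hazards. LTx affects whether and when 120 is reached.

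A reader might also apply the Background statement "In western countries, tumor progression occurs in 20–50% of cases on the transplant waiting list" to the trial and conclude that 208 patients give only 42 to 104 events. That figure describes waiting lists in general. The trial admits patients with larger single nodules than the Milan limit who are only potentially eligible for LTx, and its TTP has no stated cut-off at LTx. The figure is background and cannot serve as the trial's event fraction.

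Two further points have some force. Recurrences after LTx may count as events, since imaging continues, so treating LTx as the end of risk is somewhat pessimistic. Against that, the Background puts recurrence below 15% under the Milan criteria, which suggests few such events. The expected 48 months also leave slack beyond month 33, but no amount of time yields 120 events from 104 contributors.

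**Conclusion.** The point holds as a defect in the projection. The base of 136 patients for 120 events in 24+9 months omits the main planned exit from risk, and the text does not say whether the drop-out allowance is meant to absorb it.

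The shortfall exists on either reading of the 50%. If it includes LTx and those patients contribute nothing, as stated, about 91 events are expected by month 33 (power about 0.79). If LTx comes on top, about 82 to 52 events are expected (power about 0.75 to 0.58). The first step, from 120 to 91, comes from the drop-out statement; only the further fall is due to LTx, and its size rests on an assumed LTx median of 36 to 6 months. The plan reaches 120 events on time only if LTx is the sole loss and its median is about 9 months or longer.

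It does not follow that the trial cannot reach 120 events: that depends on transplant and drop-out rates which the document does not give or does not separate.

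**What to change.** In Sample size calculation:

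1. State the assumed LTx rate or waiting-time distribution, preferably from the participating centres, and whether the 50% drop-out includes LTx.
2. Reproject the expected events and their timing for 208 patients with LTx as a competing removal, and restate the power at the events then expected.
3. Change the final-analysis trigger to 120 events or a prespecified calendar date, whichever comes first. The final O'Brien-Fleming level should be recomputed for the events observed, by a rule fixed before unblinding.

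The cost is one recalculation and a few sentences. The stated power will probably be less favourable. The calendar fallback ensures that a final analysis takes place; it does not restore power lost through missing events.

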## Abstract

**Background:**

Disease progression of hepatocellular cancer (HCC) in patients eligible for liver transplantation (LTx) occurs in up to 50% of patients, resulting in withdrawal from the LTx waiting list. Transarterial chemoembolization (TACE) is used as bridging therapy with highly variable response rates. The oral multikinase inhibitor sorafenib significantly increases overall survival and time-to-progression in patients with advanced hepatocellular cancer.

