Transarterial chemoembolization (TACE) is the most widely usedneo-adjuvant treatment for HCC patients listed for LTx. Results of randomized controlled trials and meta-analyses of pooled data for patients with non-resectable HCC show a clear survival benefit after TACE compared with conservative management, and is therefore considered as standard of care in non-resectable HCC [6]. Two studies using TACE for bridging to LTx reported excellent outcomes [7,8]. Nevertheless, only patients with preserved liver function and asymptomatic multinodular tumors without vascular invasion or extrahepatic spread are eligible for TACE to avoid hepatic failure and severe adverse events [9]. Radiofrequency ablation was not considered because only few heterogenous uncontrolled studies suggested a slightly decrease in drop-out rate in patients treated with RFA before LTx and there is the risk of needle tract metastases.

Since HCC is generally considered to be chemoresistant, results of systemic therapy have previously been disappointing. Tumor response rates for single or multiple agent chemotherapy regimens were low without durable remission leading to a 1-year survival between 0% to 30% [10]. Increasing knowledge on the molecular pathogenesis of HCC has lead to the development of molecular targeted therapies. The oral multikinase inhibitor sorafenib (Nexavar^®^) blocks angiogenesis and cell proliferation in HCC. In patients with advanced HCC, sorafenib has shown a significant improvement in time-to-progression (TTP) and OS [11,12]. After the drug has now been approved by both, FDA and EMEA, it is the new reference standard treatment of patients with advanced HCC [12].

Evidence-based treatment for HCC relies on fewer than 100 randomized controlled trials and many observational studies. LTx with previous bridging by TACE is now accepted as the only treatment capable of definitely curing HCC but can only be applied to less than 30% of patients. Low response to TACE and progression on LTx waiting list are the major prognosis limitating factors. Sorafenib has direct inhibitory effects on tumor growth and maintains stable disease in many HCC patients. The combination of TACE and sorafenib represents a logical, new and encouraging approach for neo-adjuvant HCC therapy before LTx.

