
## Discussion

Tumor progress while waiting for LTx is common in HCC patients. Drop-out rates range between 30% to 50% [17]. The role of neo-adjuvant therapies during the time on the waiting list remains a matter of debate. Currently, TACE is the standard for bridging patients and has in addition shown good results for downstaging patients initially not eligible for LTx [18-20]. This information is based on case series, case-control studies, and cohort studies showing a 22–29% rate of complete necrosis for TACE [21-25]. Two studies employing TACE for bridging to LTx reported excellent outcome [7,8]. Nevertheless, recurrence rates were only low when applying the Milan criteria [4]. The impact of recent new treatment approaches; expanding transplant criteria and the availability of a systemic therapy with sorafenib on drop-out rate, recurrence and OS have to be assessed in randomized studies.

The HeiLivCa trial is an randomized, controlled, double-blind, multi-center trial attempting to maximize tumor growth control in patients with HCC awaiting LTx by adding sorafenib the most effective currently available systemic treatment to brdging with TACE, the current standard of care. Progression-free survival is the best surrogate endpoint in most solid malignancies, but it is a vulnerable endpoint in HCC since the underlying liver disease is a comorbidity with significant mortality that would potentially bias the evaluation of efficacy in this setting. According to the recommendation of a recent consensus conference of the AASLD and the EASLD, TTP is chosen as a more valid primary end-point. With regard to the potential side effects and possible cumulative adverse events in combination with TACE and LTx safety, efficacy and quality of life will be analyzed as secondary endpoints.

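### The sample size treats 50% of randomized patients as uninformative for TTP without separating progression and censoring from true loss, and on that premise 208 patients cannot supply 120 events

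*Protocol article*

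**What the plan says.** Under Sample size calculation, the protocol article builds its total in two steps.

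The first step has no drop-out in it. The effect is set by "assuming that median TTP is 4.5 months for the placebo-arm and 7.5 months for the sorafenib-arm". Then "A total of 120 TTP events are required for a log-rank test with an overall one-sided significance level of 0.05 and power of 0.875". The patient number that follows from these inputs is 136, and the design terms behind it are given as "Applying a 1:1 randomization, a planned accrual period of 24 months, and a follow-up period of 9 months".

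The second step adds the loss. From the surgery department's experience, "it can be expected that about 50% of the patients will drop-out after randomization. These patients do not contribute any information to the primary endpoint", and the total becomes 208 to allow for a maximum rate of 50%. No cause of drop-out is given.

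Other sections bear on what that rate can mean:
- The Abstract says that disease progression "occurs in up to 50% of patients, resulting in withdrawal from the LTx waiting list". The Background gives 20–50% for progression on the waiting list.
- The Discussion reads "Tumor progress while waiting for LTx is common in HCC patients. Drop-out rates range between 30% to 50" per cent.
- The Background says, of radiofrequency ablation, that a few studies "suggested a slightly decrease in drop-out rate in patients treated with RFA before LTx", with no cause named.
- Study objectives defines the primary event as radiological progression and censors everyone else at the last disease assessment.
- Statistical considerations puts all randomized patients in the primary efficacy population.

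**The concern.** The paragraph treats all drop-outs as if they had never been randomized. Under the plan's own endpoint definition, they can fall into three groups:

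1. Patients withdrawn from the list because the tumour progressed. They are TTP events.
2. Patients who leave without progression after at least one assessment, for example at transplantation, by death or by other withdrawal. They are censored and contribute time at risk.
3. Patients lost before any post-randomization assessment. Only they carry no information.

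The article gives one figure, 50%, and assigns all of it to group 3. Elsewhere it gives up to 50% for progression on the list, which is group 1. The direction of the error in 208 depends on the mix: the total is too small if the 50% is truly uninformative, and too large if it is mostly progression. The power of the primary analysis and the dates of the interim and final analyses move with it.

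**Working it through.** **Inputs (Sample size calculation).** Medians 4.5 and 7.5 months, so HR = 4.5/7.5 = 0.60. One-sided alpha 0.05, power 0.875, 1:1 allocation, accrual A = 24 months, follow-up F = 9 months. Exponential TTP and even accrual are assumed.

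**Step 1: the plan's own figures.** Schoenfeld events = 4(1.645 + 1.150)²/(ln 0.6)² = 120, as stated.

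With λ = ln 2/median, P(event) = 1 − [exp(−λF) − exp(−λ(A+F))]/(λA). This gives 0.934 (placebo), 0.825 (sorafenib) and a mean of 0.880. N = 120/0.880 = 136.4, which reproduces 136 with no drop-out.

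**Step 2: the 50% taken literally.**
- Informative patients: 208 × 0.5 = 104, fewer than the 120 events required.
- Expected events at month 33: 104 × 0.880 = 91.5.
- Power = Φ(√d/2 × 0.511 − 1.645): about 0.79 for d = 91.5. Even if all 104 progressed it would be about 0.83.
- Total needed: 136/(1 − 0.5) = 272.
- Loss that 208 does cover: 1 − 136/208 = 34.6%.

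**Step 3: part of the 50% is progression.** Let q be that share. The document does not give it, so the full range is shown. The informative fraction is 0.5 + 0.5q.

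| q | events at month 33 from 208 | total needed for 120 events |
|---|---|---|
| 0 | 91 | 273 |
| 0.25 | 114 | 218 |
| 0.5 | 137 | 182 |
| 0.75 | 160 | 156 |
| 1 | 183 | 136 |

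(The first row shows 273, not 272, because it starts from the unrounded 136.4.)

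At q = 1 with no other censoring, 208 patients give 60 events at about month 13.7 and 120 at about month 21.7, when 208 × 21.7/24 = about 188 are enrolled. At q = 0, 60 events come at about month 21.7 and 120 never.

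**Step 4: drop-outs are censored after some follow-up.** Take censoring as exponential with rate η, chosen so that 50% of patients, averaged over the arms, are eventually censored before progression (η = 0.119 per month; an assumption). P(event) becomes λ/(λ+η) × {1 − [exp(−(λ+η)F) − exp(−(λ+η)(A+F))]/((λ+η)A)}. For 208 patients this gives about 102 events by month 33, and about 245 patients are needed. If 40% are eventually censored, 208 patients give about 120 events.

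**The case against.** The strongest reply is that the paragraph describes a separate group. It names a different source (departmental experience), speaks of loss after randomization and calls the patients uninformative. The 136 already counts progressors, since about 88% of patients are expected to progress by month 33; drop-out is then applied on top. On this view, the paragraph may mean early transplantation or loss before any scan.

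Much of this stands, and it rules out some stronger readings that a reader might infer:

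- *That the 50% is progression withdrawal under another name.* The paragraph gives no cause. Only the Discussion sets the word beside tumour progression, and its figure comes from a cited source. The Background remark on ablation gives no cause. A shared upper value of 50% does not prove a shared quantity.
- *That the 24 + 9 months rest on this rate.* They enter only the drop-out-free 136. The final analysis is event-driven, so early arrival of 120 events would not in itself cost power. What depends on the rate is when 60 and 120 events occur with 208 patients enrolled.
- *That the label tells sites to disregard list withdrawals.* Nothing in the paragraph instructs sites, and the Investigation schedule requires imaging at the end of treatment, whether for progression or on the day of transplantation.

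The reply does not rescue the premise. Early transplantation after an assessment gives censored time, not absence of information. If the group really is uninformative, step 2 applies and 208 is too few. Calling 50% a maximum does not help, because 208 is said to accommodate that maximum.

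**Conclusion.** The point holds as an undefined and internally inconsistent drop-out assumption. Two parts need no guess about cause: the no-information statement conflicts with the censoring rule and the all-randomized analysis set, and a 50% uninformative loss leaves 104 patients for 120 required events.

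The size depends on the unstated mix. At one end, about 91 events by month 33, power about 0.79 and a need for 272 patients. At the other, 136 would suffice and 120 events would arrive at about month 21.7. Censoring of 50% lies nearer the first end, at about 102 events by month 33. These figures assume exponential TTP at the planned medians and even accrual over 24 months. The month-21.7 figure also assumes that every drop-out is a progression and that there is no other censoring, which is unlikely in patients awaiting transplantation.

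**What to change.** In Sample size calculation:

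1. Split the 50% into (a) progression, counted as a TTP event; (b) censoring after at least one post-randomization assessment, by transplantation, death or other withdrawal; and (c) loss before any such assessment. State a rate for each from the department's records.
2. Recompute expected events, power and the calendar times of 60 and 120 events for 208 patients, with (b) modelled as competing censoring and (c) removed. Dividing 136 by one minus the rate for (c) is not enough, because it makes no allowance for (b).
3. Restate whichever of the total, the power or the timing is not met.
4. Limit the no-information statement to (c).

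The cost is one rewritten paragraph and a short recalculation, from experience that the department has already drawn on. No new procedures are needed. More patients may be: even with no censoring under (b), any rate for (c) above 34.6% takes the total past 208.
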